**Methods/design:**

This prospective, single-center, randomized control trial will include 80 patients who will undergo elective PD. The patients will be randomly assigned to two groups: the experimental group that will receive esketamine (*n* = 40) and the control group (*n* = 40). In the esketamine group, the analgesic pump will be connected immediately after surgery. A solution of esketamine 1.5 mg/kg + sufentanil 2 µg/kg, diluted to 150 mL, will be administered continuously for 72 h at the background infusion and impact doses of 1 mL/h and 2 mL/time, respectively; the locking time will be 10 min. The control group will receive sufentanil 2 µg/kg that will be administered as per the esketamine group. The primary outcome will be the Hamilton Depression Scale (HAMD-17) score on the third day post-surgery (POD3). Secondary study indicators will include (1) visual analog scale (VAS) score and HAMD-17 score prior to surgery, immediately after entering the postanesthesia care unit (PACU) and 1, 2, 3, 4, and 5 days after surgery; (2) Richmond Agitation-Sedation Scale (RASS) score at 1, 2, 3, 4, and 5 days after surgery; (3) consumed doses of sufentanil and esketamine after surgery; (4) postoperative analgesia pump effective press times, rescue analgesia times, and rescue drug dosage, recording the number of rescue analgesia and rescue drug dosage at 6, 24, 48, and 72 h after the patient enters the PACU; (5) postoperative complications and adverse events; (6) postoperative hospital stay; (7) concentrations of brain-derived neurotrophic factor (BDNP), 5-hydroxytryptamine (5-HT), tumor necrosis factor (TNF-α) and interleukin-6, at 1, 3, and, 5 days post-surgery; and (8) the patient survival rate at 6 and 12 months post-surgery.

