### Data collection and follow-up period

The primary outcome measure would be the HAMD-17 score on the third postoperative day. Secondary study indicators include (1) the visual analog scale (VAS) and HAMD-17 scores prior to surgery, immediately after entering the PACU, and 1, 2, 3, 4 and 5 days after operation; (2) RASS score when the patient enters the operating room and at 1, 2, 3, 4 and 5 days after surgery; (3) the dosage of sufentanil and esketamine after surgery; (4) postoperative analgesia pump press times, rescue analgesia times, rescue drug dosage, and number of rescue analgesia times and rescue drug dosages at 6, 24, 48, and 72 h after the patient entered the PACU; (5) postoperative complications and adverse events; (6) postoperative hospital stay; (7) concentrations of brain-derived neurotrophic factor (BDNP), 5-hydroxytryptamine (5-HT), tumor necrosis factor (TNF-α), and interleukin-6 at 1, 3, and 5 days post-surgery; and (8) the patient survival rate at 6 and 12 months post-surgery. The intervention is self-regulated, and the authors are monitoring usage. Nurses in the ward will be responsible for assisting in the follow-up study of medication to ensure patient compliance. Implementing the esketamine or control group will not require alteration to usual care pathways (including the use of any medication), and these will continue for both trial arms.

Safety end-point measures will include incidence, severity, and causality of reported serious adverse events (SAEs), namely changes in the occurrence of the expected common prematurity complications and clinical laboratory test assessments, and the development of unexpected SAEs in this high-risk population. All SAEs will be followed until a satisfactory resolution or until the investigator responsible for the care of the participant deems the event to be chronic or the patient to be stable. All expected and unexpected SAEs, whether or not they are attributable to the study intervention, will be reviewed by the principal investigator and all authors to determine if there is a reasonable suspected causal relationship to the intervention. If the relationship is reasonable, SAEs will be reported to the Ethics Committee to guarantee the safety of participants.

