### Sample size calculation

The clinically meaningful beneficial effect of esketamine on the depressive symptoms of patients undergoing surgery is unclear. The minimum clinically important difference was at least 20%; however, differences in response rates range from approximately 26 to 56% among patients with major depressive disorder [17]. Therefore, we assumed that for surgical patients, the third postoperative day response rate difference would be 30% between the two groups. Likewise, for the control group, a response rate of 10% was assumed. A total of 38 patients in each group would provide 80% power with a two-sided type-I error of 0.05. The test-group-to-control-group ratio is 1. Considering an overall withdrawal rate of 5%, a sample size of 80 patients is considered adequate [10]. If data are missing, we will use multiple imputation methods to fill in according to the research needs.

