### Statistical methods

Statistical analysis will be carried out using the “intention to treat” method; all data will be collected in a single database and analyzed to evaluate any differences between the randomized groups for both primary and secondary outcomes. SAS 9.4 (SAS Institute, Cary, NC, USA) statistical software will be used for all statistical analysis. All statistical tests are two-tailed. *P*-values ≤ 0.05 will be considered statistically significant. Normally distributed data will be described as mean ± standard deviation, and the analysis of variance will be used for comparison between groups. Non-normally distributed data will be described as median (minimum–maximum), and the rank-sum test will be used for comparison between groups. The counting data are statistically described by frequency (composition ratio), and the *χ*^2^ test or exact probability method will be used for comparison between groups. The rank-sum test will be used for the inter-group comparison of grade data.

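### The stated 80% power belongs to a responder comparison (10% vs 40%), not to the declared primary outcome, the HAMD-17 score on postoperative day 3

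*Protocol article*

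**What the plan says.** The abstract and the section on data collection and follow-up agree on the primary outcome: "The primary outcome measure would be the HAMD-17 score on the third postoperative day". Neither list of secondary outcomes includes a response rate.

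The sample size section works with a different quantity. It calls the clinically meaningful effect in surgical patients unclear, cites a minimum important difference of at least 20% and response-rate differences of about 26 to 56% in major depressive disorder, and then assumes that "the third postoperative day response rate difference would be 30% between the two groups". It adds that "for the control group, a response rate of 10% was assumed". From this it concludes: "A total of 38 patients in each group would provide 80% power with a two-sided type-I error of 0.05". The allocation is equal ("The test-group-to-control-group ratio is 1"), and the total follows: "Considering an overall withdrawal rate of 5%, a sample size of 80 patients is considered adequate".

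The statistical methods section sets rules by type of data. For normally distributed data, "the analysis of variance will be used for comparison between groups". Non-normal data go to a rank-sum test, and counts to a chi-square or exact test. No test is assigned to the primary outcome by name.

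**The concern.** Power is a property of one test on one endpoint under one assumed effect. Here the effect is a difference between two proportions, while the primary outcome is a score, which under the article's own rules would go to analysis of variance or a rank-sum test. The sample size section gives no HAMD-17 mean difference, standard deviation or standardised effect, so nothing links the 80% to the primary comparison.

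At stake is the only justification offered for N. A reader who takes the section at face value will believe that the primary analysis has 80% power for a stated effect. The article does not establish that, and it does not say what difference in HAMD-17 score the trial is meant to detect.

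**Working it through.** **Inputs from the sample size section.** Control response 10%; difference 30 points, so 40% under esketamine; two-sided alpha 0.05; power 80%; ratio 1; withdrawal 5%; stated result 38 per group and 80 in total.

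**Step 1: reproduce the stated figure.** With p1 = 0.10, p2 = 0.40 and mean proportion 0.25, the pooled formula is

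n = [1.960·√(2·0.25·0.75) + 0.842·√(0.10·0.90 + 0.40·0.60)]² / 0.30² = (1.200 + 0.483)² / 0.09 ≈ 31.5.

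The continuity correction gives

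n' = (n/4)·[1 + √(1 + 4/(n·0.30))]² = (31.5/4)·(1 + √1.423)² ≈ 37.9, so **38 per group**.

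Withdrawal: 38/0.95 = 40 per group, 80 in total. Both stated figures reproduce. Other two-sided versions do not give 38: unpooled 29, arcsine 30, pooled without correction 32. The calculation is therefore a continuity-corrected comparison of two proportions, and its arithmetic is correct for that endpoint.

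**Step 2: what 38 per arm gives for a score.** The article supplies no mean difference or SD, so the standardised difference d = difference/SD is an assumption and is shown as a range. For a two-sample comparison of means with n = 38 per arm, the noncentrality is d·√(38/2) = 4.359·d with 74 degrees of freedom. Power from the noncentral t distribution, two-sided 5%:

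| d (in SD) | Power, 38 per arm |
|---|---|
| 0.3 | 25% |
| 0.4 | 41% |
| 0.5 | 58% |
| 0.65 | 80% |
| 0.8 | 93% |
| 1.03 | about 99% |

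The normal approximation gives nearly the same detectable difference: (1.960 + 0.842)·√(2/38) = 0.64 SD.

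**Step 3: where 1.03 comes from.** Suppose response meant crossing a fixed cut-off on a normally distributed scale with the same SD in both arms. The shift that turns 10% into 40% is then z(0.40) − z(0.10) = −0.253 + 1.282 = 1.03 SD. This model is illustrative. The article does not state it.

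**Step 4: in points.** At 0.65 SD, the difference detectable with 80% power is about 2.6, 3.3 or 3.9 HAMD-17 points if the SD is 4, 5 or 6. These SDs are assumed, since none is given.

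**The case against.** The strongest reply is that the mismatch may be conservative. A score usually keeps more information than a responder split, and the protocol's own 10% vs 40%, carried through the normal-shift model, gives about 99% power for the score. Even the cited minimum difference of 20%, if read as 10% vs 30% response, would correspond to about 0.76 SD and roughly 90% power. This stands as a warning against reading only the low end of the table. It does not supply the missing justification. The conversion needs a distributional model that the article does not state. The response rates are also drawn from major depressive disorder, whereas the exclusion criteria address mental illness and diagnosed, long-term treated depression. The 10% and 40% cannot be assumed to translate into a score difference in this population.

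It may also be said that the article assigns no test to the primary outcome by name, and that the fuller protocol may define response. Both are true. But a score falls naturally under the rules for measured data, and the conflict lies between two things that the article itself states, so it is not a matter of omitted detail.

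A reader might infer three stronger conclusions. The documents support none of them:

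- **That the trial is underpowered.** Without a score difference and an SD, power could be anywhere in the table.
- **That a null result would be uninterpretable.** It would be read from the estimate and its confidence interval, not from design-stage power.
- **That the endpoint could be switched unnoticed.** The abstract and the methods fix scale, form and day in the same way, so a move to response would be a visible departure from the published primary outcome.

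**Conclusion.** The point holds as a mismatch between the powered endpoint and the declared primary outcome. The 38 per group and 80 in total are correct for a continuity-corrected comparison of 10% with 40%, but that 80% power does not carry over to the HAMD-17 score on day 3.

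Power for the score comparison is not established. At 38 per arm it reaches 80% only from about 0.65 SD upwards, and across the effects considered it runs from 25% (0.3 SD) to about 99% (1.03 SD). These figures rest on a two-sample comparison of means with equal variances and 38 evaluable patients per arm, and the effect sizes are assumptions. No error of arithmetic, bias or inflation of type-I error has been shown.

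**What to change.** Keep N = 80, and settle the matter before unblinding. Recruitment is reported as ongoing, so this can still be done.

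**Preferred: keep the score as primary.**
- State that 38 evaluable patients per group give 80% power, two-sided 5%, to detect a difference of about 0.65 SD in HAMD-17 score on day 3.
- Express that difference in points, using a justified SD or one taken from blinded pooled data if enough have accrued.
- Say whether a difference of that size is clinically relevant. Without this, the statement only describes what a fixed N can detect.
- Remove response as the basis for N, or define it and list it as a secondary outcome.

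**Alternative: make response primary.** Define it and test it by chi-square or an exact test. The existing calculation then applies: at 38 per arm, 10% vs 40% has about 89% exact power by uncorrected chi-square and 83% by Fisher's exact test.

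The choice is the sponsor's. Under the preferred route the cost is a wording amendment and no extra patients, with a stated power that may look less favourable for moderate effects. The alternative also changes the published primary outcome, and that change would have to be declared.

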### Statistical methods

Statistical analysis will be carried out using the “intention to treat” method; all data will be collected in a single database and analyzed to evaluate any differences between the randomized groups for both primary and secondary outcomes. SAS 9.4 (SAS Institute, Cary, NC, USA) statistical software will be used for all statistical analysis. All statistical tests are two-tailed. *P*-values ≤ 0.05 will be considered statistically significant. Normally distributed data will be described as mean ± standard deviation, and the analysis of variance will be used for comparison between groups. Non-normally distributed data will be described as median (minimum–maximum), and the rank-sum test will be used for comparison between groups. The counting data are statistically described by frequency (composition ratio), and the *χ*^2^ test or exact probability method will be used for comparison between groups. The rank-sum test will be used for the inter-group comparison of grade data.

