### Inclusion criteria

(1) Age: 18–65 years, regardless of sex; (2) American Society of Anesthesiologists (ASA) Class I–III; (3) elective PD to be scheduled; (4) No other surgical contraindications; and (5) can clearly understand and voluntarily participate in the study and sign the informed consent form. If patients are willing to participate, they will be evaluated by Mini-Mental State Examination (MMSE), Hamilton Depression Scale (HAMD-17) [15], and Richmond Agitation Sedation Scale (RASS) [16] before surgery after they sign the informed consent form.

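### The primary POD3 HAMD-17 comparison is unadjusted and its test depends on the observed distribution; adjusting for the preoperative HAMD-17 already collected would gain precision at little cost

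*Protocol article*

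**What the plan says.** The Protocol article, Data collection and follow-up period, defines the endpoint: "The primary outcome measure would be the HAMD-17 score on the third postoperative day". The same section puts the preoperative value among the secondary indicators, as the first point of a series: "HAMD-17 scores prior to surgery, immediately after entering the PACU, and 1, 2, 3, 4 and 5 days after operation". The Inclusion criteria section confirms that consenting patients have a baseline value: "they will be evaluated by Mini-Mental State Examination (MMSE), Hamilton Depression Scale (HAMD-17) [15], and Richmond Agitation Sedation Scale (RASS) [16] before surgery".

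The Statistical methods section states that its purpose is to "evaluate any differences between the randomized groups for both primary and secondary outcomes", so it covers the primary outcome. For a score it gives two routes. For normal data, summarised by mean and standard deviation, "the analysis of variance will be used for comparison between groups". For data that are not normal, summarised by median and range, "the rank-sum test will be used for comparison between groups". The section mentions no covariate, change score or longitudinal model.

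**The concern.** The preoperative score is measured before the analgesic pump is connected, so treatment cannot affect it. If it predicts the day-3 score, including it in the model removes between-patient variation that the unadjusted test leaves in the error term. The stated method leaves that information unused in a trial of only 80 patients.

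Two further points follow.

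- **Effect measure.** The test is picked by the observed distribution, so it is not settled in advance whether the primary result is a difference in mean HAMD-17 points or a comparison of ranks.
- **Role of baseline.** Apart from the assessment at entry, the only role the article gives the preoperative HAMD-17 and VAS is as secondary indicators. A pre-treatment value cannot be an outcome.

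Precision matters here because the sample size was derived for a response rate. Power for the comparison of scores is therefore not established anywhere in the article.

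**Working it through.** **Inputs from the Protocol article (Sample size calculation).** 38 per arm, two-sided alpha 0.05, 80% power, response 10% against 40%, 5% withdrawal, 80 in total.

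**Assumed, because the article gives no value.** The correlation r between preoperative and day-3 HAMD-17 (0.2 to 0.6), and a true difference of 0.5 SD.

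**1. The plan's own figure.** Two-proportion formula with mean proportion 0.25:

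n = [1.96·√(2·0.25·0.75) + 0.842·√(0.1·0.9 + 0.4·0.6)]² / 0.3² = 31.5

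With continuity correction: n′ = (31.5/4)·[1 + √(1 + 4/(31.5·0.3))]² = 37.9, so 38 per arm. Then 38/0.95 = 40 per arm, 80 in total. The stated size reproduces, but for a responder proportion and not for a mean score.

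**2. Effect of adjustment on normal-theory assumptions.** ANCOVA multiplies the error variance by 1 − r². Power comes from the noncentral t distribution with noncentrality (0.5/√(1 − r²))·√(38/2), on 74 df unadjusted and 73 df adjusted. The detectable difference is for 80% power.

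| r | 1 − r² | Noncentrality | Power at 0.5 SD | Detectable difference | Equivalent n per arm, 38/(1 − r²) |
|---|---|---|---|---|---|
| unadjusted | 1 | 2.18 | 57.6% | 0.651 SD | 38 |
| 0.2 | 0.96 | 2.22 | 59.3% | 0.638 SD | 39.6 |
| 0.3 | 0.91 | 2.28 | 61.6% | 0.621 SD | 41.8 |
| 0.5 | 0.75 | 2.52 | 70.0% | 0.564 SD | 50.7 |
| 0.6 | 0.64 | 2.72 | 76.7% | 0.521 SD | 59.4 |

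**3. Simulation with normal data.** 4,000 runs per setting, 38 per arm, difference set so that the unadjusted test has about 80% power. ANCOVA reached 82%, 90% and 98% at r = 0.3, 0.5 and 0.7. The t-test, and a t-or-rank-sum choice made by a normality test, both stayed at about 80%. Type I error was about 5% for all three. The lost power comes from omitting baseline. The data-driven choice of test cost almost none.

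**4. Chance imbalance.** The standard error of the baseline mean difference is √(2/38) = 0.229 SD. An imbalance of one standard error shifts the expected unadjusted day-3 difference by r × 0.229, which is 0.115 SD at r = 0.5. Only this correlation-weighted part carries over.

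**5. Simulation with skewed scores.** Assumed lognormal integer scores, 38 per arm.

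- Log-SD 0.8, r = 0.3: raw-score ANCOVA had about 69% power against about 77% for the unadjusted rank-sum test.
- Log-SD 0.8, r = 0.5: the two were close (76% against 77%). ANCOVA was ahead at 0.6.
- Log-SD 0.6: rank-sum led at r = 0.3 (78% against 75%), tied at 0.4 and fell behind from 0.5.
- Rank ANCOVA, which adjusts ranks for baseline ranks, had more power than the rank-sum test in every setting tried.

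**The case against.** - **The article is condensed.** The full protocol is offered on request and any analysis plan is not shown. The Statistical methods paragraph is generic by data type and does not name HAMD-17, so an unseen document could add a covariate. This stands as a caution. But the article states a method for the primary outcome, and that method is unadjusted; the point improves a stated choice and does not complain of missing detail.

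- **Validity.** A reader might infer that the planned result is biased, or that any baseline imbalance passes fully into the day-3 difference. The documents do not support this. Allocation is randomised 1:1, the tests keep their error rate, and only the correlation-weighted share of an imbalance carries over.

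- **Size.** A reader might quote the gain at r = 0.5, about 13 patients per arm (50.7 − 38), as a fact. It is not one: the article gives no correlation, no SD and no target difference in points. Diagnosed, drug-treated depression is excluded and major surgery separates the two measurements, so a low correlation is plausible. At r of 0.2 or less the gain is under 2 percentage points.

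- **Raw-score ANCOVA is not always the more powerful test.** This stands. With strong skew and a weak correlation, the unadjusted rank-sum test can beat it, so it would be wrong to say that the plan gives up power for nothing in every case. Adjustment itself survives the objection, because rank ANCOVA beat rank-sum throughout.

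- **Preoperative scores as outcomes.** A reader might infer that a preoperative between-group test is planned. The article lists one measurement schedule and specifies no such test; at most, the generic methods sentence implies it.

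- **The endpoint itself is unsettled.** The sample size uses a response rate while the named outcome is a score. If that conflict were resolved towards response, linear ANCOVA would not apply.

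**Conclusion.** The point holds as one of efficiency and prespecification. The stated primary comparison is valid, but it leaves an already collected baseline score unused and lets the data decide the effect measure. With 38 per arm and normal-theory assumptions, power at an assumed 0.5 SD goes from 58% to 59%, 62%, 70% or 77% at assumed correlations of 0.2, 0.3, 0.5 or 0.6. The benefit therefore runs from negligible to about 19 percentage points (76.7 − 57.6), and the documents cannot say where in that range it lies. The conclusion assumes that the day-3 score remains the primary outcome. It should be changed, but it does not threaten the validity of the trial.

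**What to change.** Before unblinding, amend the Statistical methods section as follows:

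- Name one primary analysis: ANCOVA of day-3 HAMD-17 on treatment group with preoperative HAMD-17 as covariate, reporting the adjusted mean difference in points and its 95% CI. Remove the choice of test by distribution for this outcome.
- Prespecify rank ANCOVA on the same baseline as the sensitivity analysis, in place of the unadjusted rank-sum test, because scores may be skewed.
- Describe preoperative HAMD-17 and VAS as baseline covariates, and take them out of the indicators compared between groups.

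No new data or patients are needed. The cost is a documented amendment to the primary analysis while recruitment is under way, and the gain will be small if the correlation turns out low.

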## Discussion

The study hypothesizes that the postoperative HAMD-17 and VAS scores, incidence of postoperative adverse reactions, and concentration of the serum markers BDNP, 5-HT, TNF α, and IL-6 will be lower than those in the control group. The HAMD-17, which was developed by Hamilton in 1960 [18], is the most used scale in the clinical evaluation of depression and can accurately assess the depression status of adult patients [15, 19]. Pain is an independent risk factor for depression [8, 9]. The analgesic effect of esketamine and the effect of treating depression can effectively reduce the postoperative VAS and HAMD-17 scores of patients.

Ketamine is an NMDA receptor antagonist, a widely used anesthetic [20] for the treatment of depression [21]. The most important brain regions associated with depression are the amygdala and hippocampus [22]. The amygdala converts negative information (e.g., anxiety and depression) into neural signals in the brain and is closely related to behavior and mood. Alterations in hippocampal architecture and synaptic remodeling are strongly related to the onset of depression and the effects of antidepressants. Depression is usually caused by reduced levels of monoamine neurotransmitters in the brain, such as serotonin (5-HT). 5-HT is an important neurotransmitter in the brain, with levels closely related to the pathogenesis of depression [23]. BDNF is the most abundant neurotrophic factor in the body, and its association with depression has also recently been confirmed [24, 25]. Moreover, BDNF polymorphisms are associated with the antidepressant efficacy of ketamine in depressed patients [24]. TNF-α and IL-6 are inflammatory indicators and are strongly correlated with postoperative depression [26].

The NMDA receptors are closely related to the development of central sensitization in the dorsal horn neurons [27, 28], which are responsible for transmitting pain signals. Central sensitization occurs with persistent nociceptive inputs caused by inflammation or injury, leading to persistent and gradually exacerbated pain, hyperalgesia, abnormal pain, relative unresponsiveness to opioids in chronic pain, and severe visceral pain [29]. Binding of ketamine to NMDA receptors may reverse these phenomena. Acute and chronic pain are known risk factors for the onset of postoperative depression [30]. Therefore, well-established postoperative analgesia is a key strategy to reduce the incidence of postoperative depression. The follow-up period of this experiment is long and there is a high risk of loss of follow-up. Long-term and effective communication between researchers, patients, and their families is the key to solving this difficulty.

